**Sample size estimation**

Sample size estimation in this RCT is based on the expected improvement of the balance ability in 12-week TCC exercise in college students. The data of our preliminary experiment showed that the means and standard deviation of the balance ability (presented by motion of ellipse area which tested by standing with eyes closed on the flat of Pro-kin system) in the college students was 531.25 and 173.78. 15% improvement of balance ability will be expected after 12 week intervention. According to the same size of the estimation formula   (set α= 0.05, β= 0.10). It is estimated that a sample size of 93 participants per group will be required, considering 10% drop-out and exit. Therefore, we will recruit approximately a total of 206 participants, 103 participants in each group.

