**Outcomes measurement**

The primary or secondary outcomes will be tested at baseline, 12 and 24 week post-intervention. A schedule of assessments that will be carried out is listed in Table 1. The balance ability and [lower](app:ds:lower) [limbs](app:ds:limbs) proprioception will be assessed at Rehabilitation Hospital Affiliated to FJTCM by three experienced [rehabilitation](app:ds:rehabilitation) [therapist](app:ds:therapist)s who do not involve in this study. The physical fitness test, [cardio-pulmonary](app:ds:cardio-pulmonary) [function](app:ds:function), flexibility, vital capacity, and weight will be conducted at campus gymnasium by the physical education teachers. The outcome assessors of this trial will be in charge of the assessment of relevant psychology scales including self-efficiency, attention, stress self-esteem, and quality of sleep.

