**Statistical analyses plan**

SPSS21.0 statistical analysis software will be used to analyze data. The primary outcomes of participants who are randomized and received at least one treatment week will be carried by the intention-to-treat (ITT) analysis. Per-protocol subjects analysis（PPS）of the primary outcomes will include participants who have completed the 24-week study without major protocol violations and have compliance rate > 85%. We will compare the results of the ITT with that PP analysis to check-up whether the results are consistent or not. The continuous variables will be expressed using means with standard deviations or medians with ranges. For the variables with a normal distribution, statistical comparisons between the groups will be made by using a *t* test. If the variables have a non-normal distribution of ordinal level, statistical comparison between groups will be made using the Mann-Whitney *U* test. Measures with a discrete distribution will be expressed as percentages and analyzed by theχ2 or Fisher’s exact test as appropriate. A general linear model or Logistic regression model will be applied to adjust the confounding influence if necessary. The *p* value is less than or equal to 0.05 will be considered as a test by the difference has statistical significance.

Participants’ recruitment

Eligible patients n=206

Baseline assessment

Exclusion (reasons): n=

Not meeting inclusion criteria: n=

Declined to participate: n=

Other reasons: n=

Randomization allocation

TCC training group

n=103

Control group

n=103

Drop out (reasons): n=

TCC training group: n=

Control group: n=

Outcome assessment after intervention: balance ability, lower limbs proprioception, flexibility, physical fitness, self-efficiency, psychological symptoms ,attention, stress, self-esteem, mood and mindfulness, quality of life, quality of sleep, safety outcomes.

Follow up for 12 weeks

Lost to follow up: n=

TCC training group: n=

Control group: n=

Outcome assessment after follow-up period

Included analysis: n=

TCC training group: n=

Control group: n=

Statistic analysis

Excluded from analysis: n=

TCC training group: n=

Control group: n=

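### The group comparison is a t or Mann-Whitney test with no baseline covariate, and adjustment is left conditional, although every efficacy outcome has a pre-randomisation value; a pre-specified ANCOVA would be more precise at no extra cost

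*Protocol*

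**What the plan says.** The Statistical analyses plan section of the Protocol names the tests. Normal variables get a t test, introduced by the words "For the variables with a normal distribution, statistical comparisons between the groups will be made by using a"; variables that are not normal go to the Mann-Whitney U test instead. Neither sentence mentions a baseline value, and neither says whether the variable compared is the post-intervention value or the change from baseline.

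Modelling appears in one further sentence: "A general linear model or Logistic regression model will be applied to adjust the confounding influence if necessary". It lists no covariates, does not say what makes adjustment necessary, and does not say which result is primary if both are produced.

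Baseline values will be available. Outcomes measurement states that "The primary or secondary outcomes will be tested at baseline, 12 and 24 week post-intervention", and Table 1 marks every listed efficacy outcome in the pre-enrolment column (weeks -2 to -1) as well as at weeks 13 and 25. Only safety outcomes and diaries have no baseline entry, as one would expect. Randomization and allocation concealment places randomisation after the baseline assessment, so these values are legitimate covariates.

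**The concern.** In a randomised trial the sound reason to adjust for a baseline measurement is precision. The baseline of an outcome usually explains part of the variation in its later value, and removing that part narrows the confidence interval without a single extra participant. The plan pays for the baseline assessments and then names tests that do not use them as a covariate.

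The stated ground for adjustment, confounding, fits a randomised comparison poorly. Randomisation removes systematic baseline confounding, so what remains is chance imbalance. With neither a trigger nor a priority rule, the Protocol leaves open which of two results (adjusted or unadjusted) is the reported finding. The question recurs for each of the seven primary outcomes.

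**Working it through.** **Inputs.** Sample size estimation gives a mean and SD of balance (ellipse area, eyes closed) "in the college students was 531.25 and 173.78". The effect is given by "15% improvement of balance ability will be expected after 12 week intervention", and the error rates by "set α= 0.05, β= 0.10". The number needed is 93 per group, raised to 103 for 10% drop-out. Sidedness is not stated; I take two-sided 0.05. The baseline-outcome correlation ρ is not in the Protocol; I assume 0.3, 0.5 and 0.7. For the adjusted and change-score analyses I also assume equal SDs at baseline and follow-up.

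**Effect size.** Difference = 0.15 × 531.25 = 79.69. Standardised difference d = 79.69 / 173.78 = 0.459.

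**The plan's own figure.** For a two-sided t test with 90% power, n = 2 × (173.78 × (1.960 + 1.282) / 79.69)² ≈ 100 per group (101 by the exact t calculation), or 112 after dividing 100 by 0.9. The stated 93 and 103 are not both reached by any variant tried. A one-sided test needs 83 by exact t, which becomes 93 after drop-out, but the step to 103 would then count drop-out twice. This is a separate matter. I keep 93 evaluable per group because the Protocol states it.

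**Formulas.** Effective standardised difference:
- t test on post-values: d
- ANCOVA on baseline: d / √(1 − ρ²), because the residual variance falls by the fraction ρ²
- t test on change scores: d / √(2(1 − ρ))

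Power is then from the noncentral t distribution. The one degree of freedom that ANCOVA uses for the covariate does not alter the first decimal.

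**Results, 93 per group, two-sided 0.05.**

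| ρ (assumed) | Variance removed by ANCOVA | t test, post-values | ANCOVA: effective d, power | Change scores: effective d, power |
|---|---|---|---|---|
| 0.3 | 9% | 87.5% | 0.459/0.954 = 0.481, 90.3% | 0.459/1.183 = 0.388, 74.8% |
| 0.5 | 25% | 87.5% | 0.459/0.866 = 0.529, 94.9% | 0.459/1.000 = 0.459, 87.5% |
| 0.7 | 49% | 87.5% | 0.459/0.714 = 0.642, 99.2% | 0.459/0.775 = 0.592, 98.0% |

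ANCOVA gains 2.8, 7.4 and 11.7 points over the t test on post-values. The number per group for 90% power falls from 101 to 92, 76 and 52. Were all 103 per group evaluable, power would be 90.6% unadjusted against 93.0%, 96.6% and 99.6%. Change scores never beat ANCOVA, and at ρ = 0.3 they do worse than ignoring the baseline.

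**The open choice of model.** A null simulation (20,000 runs, 93 per group, threshold 0.05) that always reports the smaller of the t-test and ANCOVA p values rejects in 6.5%, 7.4% and 8.0% of runs at ρ = 0.3, 0.5 and 0.7. A second null simulation (10,000 runs) that adjusts only after a significant baseline difference rejects in 4.7%, 4.6% and 3.4%. The consequence therefore depends on a rule that the Protocol does not give.

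**The case against.** The strongest reply is that nothing here is invalid. A two-sample t test is unbiased under randomisation, chance baseline differences are already reflected in its standard error, and the sample size inputs contain no correlation, so an unadjusted test is consistent with the design. Covariates and triggers are often settled in a statistical analysis plan, which may exist. All of this is fair, and it limits the point to precision and pre-specification. It does not remove it: the Protocol does more than stay silent, since it names the tests and makes adjustment conditional.

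The size of the gain is also uncertain. It depends on an assumed ρ, and the balance effect size cannot stand for outcomes as different as flexibility and a symptom scale. That stands.

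Three stronger readings are tempting, and the Protocol does not support them:
- **That the test certainly ignores the baseline.** Post-values are the natural reading, but a t test on change scores is not excluded.
- **That adjustment will follow an observed imbalance.** The wording allows it, but no trigger is stated.
- **That the type I error is inflated.** The 6.5% to 8.0% applies only if the smaller p value is always reported, which nothing in the text says. The Blinding section keeps groups coded until the analysis is complete. That does not prevent picking the smaller p value, but it limits choosing by direction. Choosing between t and Mann-Whitney by distribution is itself a rule written in advance, though without a stated criterion.

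**Conclusion.** The point holds as one of efficiency and pre-specification. The planned comparison is valid, but a baseline-adjusted model is at least as precise under either reading of the t test. At 93 per group, d = 0.459 and two-sided 0.05, the gain over post-values is about 3 points of power at ρ = 0.3, 7 at 0.5 and 12 at 0.7. Over change scores it is about 16, 7 and 1 points. On the Protocol's inputs the t test on post-values falls short of the intended 90% at 93 per group, and a correlation of only 0.3 would be enough to reach it. These figures rest on the assumed correlations, equal SDs at the two times and a two-sided test, and they concern the balance outcome only.

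Separately, with no trigger and no priority, the Protocol does not settle whether the adjusted or the unadjusted result is primary. That is an ambiguity to close, and it is no evidence of selective reporting.

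**What to change.** Pre-specify, as the primary analysis of each continuous efficacy outcome, an ANCOVA of the end-of-training value (week 13 in Table 1) on group and that outcome's own baseline value. Analyse the end-of-follow-up value by the same model. Report the adjusted mean difference with its 95% confidence interval.

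Decide any transformation (for example the log of ellipse area) or use of robust standard errors in advance, outcome by outcome, and not after inspecting residuals; otherwise one data-dependent switch replaces another. Remove the condition and the reference to confounding from the adjustment sentence. Keep the t or Mann-Whitney test as a sensitivity analysis, and state whether it is applied to post-values or to change scores.

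The cost is a change of wording, to be made before outcome data are examined by group. It needs no extra participants, visits or measurements, and the general linear model is already named in the plan.

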**Follow-up period**

During the 12-week follow-up period, all of the participants will return to their original lifestyles, but be required to record their daily physical activities or sport information. The primary outcomes will be re-measured at end of follow-up period.

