**Primary outcome measures**

1. Balance ability

It will be tested by standing with eyes open for 30 seconds and standing with eyes closed for 30 seconds via Pro-kin system(Machine type: produce by *Italy Tecnobody. S.R.L company, model PK254P*)

2. Lower [limbs](app:ds:limbs) proprioception: both left and right legs will be tested via Pro-kin system (*Machine type: produce by Italy Tecnobody. S.R.L company, model PK254P*).

3. Flexibility: will be tested with Sit and Reach flexibility test equipment (Machine type: *Beijing ZhongTi Tongfang Co., Ltd., model CSTF-TQ-5000*).

4. Self-efficiency: *The* *Self-Regulatory Self-Efficacy Scale* will be used to test self-efficiency.

5. Psychological symptom score: will be assessed by using *SCL-90 scale* .

6. Attention span: will be assessed with *Schulte grid (8*8) scale.*
7. Stress: will be measured with *Chinese Perceived Stress Scale* .

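### Seven unranked primary outcomes, with no primary time point, are each judged at p ≤ 0.05, while the trial is sized on one of them

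*Protocol*

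**What the plan says.** Under Primary outcome measures the protocol numbers seven outcomes: balance, lower-limb proprioception, flexibility, self-efficacy, SCL-90 symptom score, attention span and, as the last entry, "7. Stress: will be measured with" a perceived stress scale. None is placed above the others.

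Two of the seven have two sub-measures. For balance: "It will be tested by standing with eyes open for 30 seconds and standing with eyes closed for 30 seconds via Pro-kin system". For proprioception: "both left and right legs will be tested via Pro-kin system". That section names no Pro-kin parameter for either.

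On timing, Outcomes measurement states: "The primary or secondary outcomes will be tested at baseline, 12 and 24 week post-intervention". Follow-up period adds: "The primary outcomes will be re-measured at end of follow-up period". Table 1 places these assessments at weeks 13 and 25. Neither is called the primary time point.

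The Statistical analyses plan section compares the groups variable by variable (t test or Mann-Whitney) and sets one threshold for all of them: a p "value is less than or equal to 0.05 will be considered as a test by the difference has statistical significance". It gives no order of testing and does not say how many primary outcomes must succeed.

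Sample size estimation uses one measure: "Sample size estimation in this RCT is based on the expected improvement of the balance ability in 12-week TCC exercise in college students", with balance "presented by motion of ellipse area which tested by standing with eyes closed on the flat of Pro-kin system". It sets α = 0.05 and β = 0.10.

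**The concern.** A threshold of 0.05 limits the error of one test. Here it is offered to seven outcomes of equal standing, at two times, and the protocol does not say which result decides the trial. If one significant primary outcome is enough, the chance of a positive trial under no effect exceeds the α used for the sample size. The 90% power describes only the sized measure, so a reader cannot tell what the trial as a whole is powered to show. Because no endpoint or time point comes first, the headline result could be chosen after the data are seen. All seven outcomes are prespecified, so such a choice would be visible, but nothing in the text rules it out.

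**Working it through.** **Inputs.** Mean 531.25, SD 173.78, 15% improvement, α = 0.05, β = 0.10, 10% drop-out, 93 and then 103 per group (Sample size estimation). Seven outcomes, two of them with two sub-measures (Primary outcome measures). Two post-baseline times (Outcomes measurement, Follow-up period, Table 1). Threshold 0.05 per comparison (Statistical analyses plan). Correlations between outcomes are not given and are assumed below.

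**The plan's own figure.** Difference = 0.15 × 531.25 = 79.69; standardised d = 79.69/173.78 = 0.459. With n = 2(z_α + z_β)²/d² per group:
- One-sided α: 2(1.645 + 1.282)²/0.459² gives 82 (83 with the t distribution). Dividing by 0.9 gives 92 (93 with t), which matches the stated 93.
- Two-sided α: 2(1.960 + 1.282)²/0.459² gives 100, or 112 after drop-out. This matches neither 93 nor 103.

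The stated 93 thus fits a single comparison at an undivided 0.05. The protocol does not state whether the test is one- or two-sided. Read as two-sided, power for that comparison is about 88% with 93 per group and 91% with 103.

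**Number of tests.** Seven outcomes at one time = 7. Splitting balance and proprioception adds two = 9. Seven outcomes at two times = 14. Nine measures at two times = 18.

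**Family-wise error, independent tests.** 1 − 0.95^k:
- k = 7: 1 − 0.698 = 30.2%
- k = 9: 1 − 0.630 = 37.0%
- k = 14: 1 − 0.488 = 51.2%
- k = 18: 1 − 0.397 = 60.3%

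**Family-wise error, correlated tests.** Take Z_i = √ρ·F + √(1 − ρ)·E_i, with F and E_i independent standard normal, and find P(max|Z_i| > 1.96). Numerical integration gives the values below; simulation with 200,000 draws agrees to about one percentage point.

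| Tests | ρ = 0 | ρ = 0.3 | ρ = 0.5 | ρ = 0.8 |
|---|---|---|---|---|
| 7 | 30% | 27% | 23% | 15% |
| 9 | 37% | 33% | 27% | 17% |
| 14 | 51% | 44% | 35% | 20% |
| 18 | 60% | 51% | 40% | 22% |

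A more structured 18-test case, with assumed correlations of 0.6 within an outcome, 0 to 0.5 between outcomes and 0.5 to 0.7 between times, gives 41% to 56%.

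**Power if all seven stay primary.** The strictest Holm step is 0.05/7 = 0.00714, two-sided, with critical z = 2.690. The expected z is d√(n/2):
- n = 93: 0.459 × √46.5 = 3.127. Power = Φ(3.127 − 2.690) = 67% (66% with t).
- n = 103: 0.459 × √51.5 = 3.291. Power = Φ(3.291 − 2.690) = 73% (72% with t).

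Holding 90% at that step needs 2(2.690 + 1.282)²/0.459², or 151 per group, and 168 after 10% drop-out.

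**The case against.** The strongest reply is that a multiplicity procedure commonly sits in a SAP, and the SAP is not at hand. That stands as far as it goes: the absence of an adjustment method is not the point here. The point is what the protocol itself fixes, namely seven unranked primaries, a 0.05 rule for each comparison, and a sample size computed at an undivided 0.05 for one of them. A SAP that divided α would depart from that rule and lower the stated power.

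Several stronger readings are tempting, and the documents do not support them:
- **That the error is 30% to 60%.** Those are the independence values for 7 and 18 tests. The extra tests come from the same students measured with eyes open and closed, on both legs, and at two times. They are unlikely to be independent, so 60% is an upper bound for 18 tests.
- **That the protocol prescribes 18 tests.** It does not say that legs and eye conditions are analysed separately, or that each time point carries its own decision. The sizing is tied to 12 weeks, and the follow-up measurement can be read as subsidiary. Seven is the only firm count.
- **That a false positive is likely.** For 7 or 9 tests no figure above exceeds 37%. Among the common-correlation figures, only the counts that include both time points pass 50%, and only when correlation is low.
- **That one success is declared sufficient.** The protocol states no such rule. Separate conclusions by domain are a possible reading of its Objective. If all seven had to be significant, the inflation would vanish, but the 90% power would no longer describe the chance of trial success. No such rule is stated either.
- **That sizing on one measure is an error.** It is ordinary practice. The difficulty is that this measure is not then singled out as the endpoint that decides the trial.

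**Conclusion.** The point holds. Followed as written, the protocol's α of 0.05 is not the error rate of a positive primary result. For the firm count of seven outcomes at one time point, the error is about 15% to 30% across assumed correlations of 0.8 down to 0, instead of 5%. If sub-measures and both time points are each tested, it is about 22% to 60%. These figures assume that TCC affects none of the outcomes and that any one significant primary outcome counts as success. The correlations are assumptions throughout. The size is uncertain, but no correlation examined brings it near 5%. This should be settled before the data are analysed, because the trial's main conclusion depends on it.

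**What to change.** Name one primary endpoint and one primary time point: Pro-kin ellipse area, standing with eyes closed, at the end of training (Table 1 week 13). Test it at 0.05, stating whether the test is one- or two-sided. This is the measure on which the trial was sized. Make the other six outcomes, the eyes-open condition and all week-25 results secondary, and either test them with Holm or report them as supportive with confidence intervals.

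This needs changes of wording only, with no extra participants or data. Its real cost is that no psychological outcome remains primary, although the Objective covers mental as well as physical health.

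If the sponsor wants to keep all seven as primary, apply Holm across the seven at week 13, say how the two balance conditions and the two legs each become one measure, and restate the power. At the strictest step, two-sided, power for the sized outcome is about 66% with 93 per group and about 73% with 103, against about 88% with 93 at an unadjusted two-sided 0.05. Part of the gap between the planned 90% and 66% therefore comes from the two-sided reading and not from multiplicity.

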**Recruitment**

**Allocation and intervention**

**Follow up**

**Analysis**

**Figure 1 Flow diagram of participants**

| **Table 1 Trial Processes Chart**   | Items | Before enrollment (week) | TCC training phase(week) | Training end (week) | Follow-up (week) | Follow-up end(week) | | --- | --- | --- | --- | --- | --- | | **-2-(-1)** | **1-12** | **13** | **13-24** | **25** | | Inclusion criteria | * |  |  |  |  | | Exclusion criteria | * |  |  |  |  | | Informed consent | * |  |  |  |  | | Baseline | * |  |  |  |  | | Randomization | * |  |  |  |  | | Self-esteem | * |  | * |  | * | | Mood and mindfulness | * |  | * |  | * | | Self-efficiency | * |  | * |  | * | | Psychological symptom score | * |  | * |  | * | | Stress test | * |  | * |  | * | | Flexibility | * |  | * |  | * | | Step testing | * |  | * |  | * | | Rest heart rate | * |  | * |  | * | | Vital Capacity | * |  | * |  | * | | Systolic [blood](app:ds:blood) [pressure](app:ds:pressure) | * |  | * |  | * | | [Diastolic](app:ds:diastolic) [blood](app:ds:blood) [pressure](app:ds:pressure) | * |  | * |  | * | | Balance | * |  | * |  | * | | [Lower](app:ds:lower) [limbs](app:ds:limbs) proprioception | * |  | * |  | * | | Attention span | * |  | * |  | * | | Quality of life | * |  | * |  | * | | Quality of sleep | * |  | * |  | * | | Safety outcomes |  | * |  | * |  | | Self-report diaries |  | * |  | * |  | |
| --- | --- | --- | --- | --- | --- | --- | --- | --- | --- | --- | --- | --- | --- | --- | --- | --- | --- | --- | --- | --- | --- | --- | --- | --- | --- | --- | --- | --- | --- | --- | --- | --- | --- | --- | --- | --- | --- | --- | --- | --- | --- | --- | --- | --- | --- | --- | --- | --- | --- | --- | --- | --- | --- | --- | --- | --- | --- | --- | --- | --- | --- | --- | --- | --- | --- | --- | --- | --- | --- | --- | --- | --- | --- | --- | --- | --- | --- | --- | --- | --- | --- | --- | --- | --- | --- | --- | --- | --- | --- | --- | --- | --- | --- | --- | --- | --- | --- | --- | --- | --- | --- | --- | --- | --- | --- | --- | --- | --- | --- | --- | --- | --- | --- | --- | --- | --- | --- | --- | --- | --- | --- | --- | --- | --- | --- | --- | --- | --- | --- | --- | --- | --- | --- | --- | --- | --- | --- | --- | --- | --- | --- | --- | --- | --- | --- | --- | --- | --- | --- |
